#### Microbiome characterization

2.8.2

1Blood Lactococcus and other microbial DNA raw data processing

Raw Illumina sequencing reads will be processed using Readfq to remove poor quality bases (threshold ≤38 bp), reads with excessive N bases, and significant adaptor overlaps. Host-derived reads will be filtered using Bowtie2.2.4 software with parameters: -end-to-end, --sensitive, -I 200, -X 400 [26,27].2Metagenome assembly

Clean reads will be assembled into Scaffolds using MEGAHIT with -presets meta-large option. Scaffolds will be converted into scaftigs by removing N-containing regions [28,29]. Reads will be mapped back to scaffolds using Bowtie, and fragments <500 bp will be excluded from further analysis [30,31].3Gene prediction and abundance calculation

Scaftigs ≥500 bp will be analyzed for open reading frames (ORFs) using MetaGeneMark, filtering out those <100 nt [32,33]. CD-HIT will be used to cluster and remove redundant genes, generating a non-redundant gene catalogue [34,35]. Clean reads will be mapped to this catalogue using Bowtie2, and genes with ≤2 mapped reads will be excluded. Gene abundances will be calculated as described previously [31].4Taxonomy prediction

Unigenes will be taxonomically annotated using the Kraken2 database [36], with further validation against the NCBI NR database [37]. The LCA algorithm in MEGAN [38] will be used for accurate species-level assignment. Taxonomic profiles will include relative abundances and gene counts for all taxa, with specific attention to YDB.

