An emerging strategy for microbiome analysis involves profiling the blood microbiome, a novel approach that captures microbial signals from multiple body compartments, particularly the gut [10]. The blood microbiome comprises circulating microbial DNA (cmDNA), which consists of fragmented genetic material from microorganisms rather than intact, viable cells. The precise mechanisms through which microbial DNA enters the bloodstream remain unclear [11], though the gastrointestinal tract is considered a major source, especially in the context of impaired gut barrier integrity, a feature commonly observed in chronic diseases. Blood-derived microbiome signatures have demonstrated potential as non-invasive biomarkers for a range of conditions, including diabetes, cardiovascular disease, and cancer, with preliminary evidence suggesting they may even distinguish among different cancer types [10,12]. Despite this promise, the field is subject to ongoing debate, largely due to technical limitations in bioinformatic analysis and the risk of contamination or other artifacts [13,14], underscoring the need for rigorous proof-of-concept studies. These challenges highlight the urgent need for rigorous, well-controlled proof-of-concept studies, a gap that our current research aims to address.

Building on previous findings, we observed that *Lactococcus lactis*, a dairy-dependent intestinal bacterium, is undetectable in human stool within four days of dairy withdrawal, but reappears rapidly upon dairy reintroduction [15,16]. Although the precise half-life of bacterial DNA in human blood is unknown, studies on cancer- and fetal-derived cell-free DNA suggest it is typically less than 24 h [17]. Based on this, a 10-day period of dairy exclusion should markedly reduce cmDNA from milk-associated microbes, with subsequent reemergence following dairy intake.

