Because the blood microbiome may be less than 5 % of the entire blood DNA, interpretation of such low microbial biomass is challenged by potential environment contamination (e.g., lab equipment and kitome) [22,23]. In addition, the definition of a core blood microbiome is further complicated by that the assembled genomes of many bacteria (especially older assemblies) are contaminated by human DNA sequences, leading to false-positive results. The latter issue is considered the biggest problem in the analysis and interpretation of blood microbiomes [14]. The current study, because of its longitudinal character and its reliance on the introduction of defined species with relatively novel assemblies in the database, is designed to provide of proof-of-principle on whether these problems can be overcome. Further, additional power will be added to the current study by introduction of additional controls: we will include a series of reference controls designed to account for all potential sources of contamination and misinterpretation described above (Fig. 3).2DNA extraction and shotgun sequencing

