To minimize the cross-contamination of kitome from different DNA isolation kits, we will choose the same kits from same company to isolate DNA from all samples types, including feces and blood. The analysis of the cmDNA may follow a slightly modified version of our previously published pipeline [24]. Briefly, fasting blood (5 mL) will be collected by a certified phlebotomist at each time point. Of this, 2.5 ml will be used for DNA extraction and remainder for plasma collection. The samples will be stored at −80 °C until further processing. The blood YDB and other microbial DNA will be assessed by sequencing following the steps below: 1) Blood DNA will be extracted by a commercial available kit or a modified cetyltrimethylammonium bromide (CTAB) method [25]. Briefly, 1000 μl of CTAB lysis buffer at 65 °C with lysozyme will be added to 250 μl of the whole blood and gently inverted. After centrifugation at 12 000 rpm for 10 min, the supernatant will be transferred into a 2.0 ml tube containing phenol/chloroform/isoamyl alcohol (25:24:1). Following another centrifugation, the supernatant will be moved into a new tube, mixed with 24:1 isoamyl alcohol and centrifugated again. The supernatant will be mixed with isopropanol, incubated at −20 °C, and discarded. The precipitate will be washed with 1000 μl of 75 % ethanol twice, dried and dissolved in dd H_2_O. Finally, 1 μl of RNase A will be added, and the mixture will be incubated at 37 °C for 15 min; 2) DNA degradation will be monitored on 1 % agarose gels, and concentration will be measured using Qubit® dsDNA Assay Kit in Qubit® 2.0 Flurometer (Life Technologies, CA, USA). Samples with an OD value between 1.8 and 2.0 and contents above 1ug will be used for library construction; 3) Sequencing libraries will be created using NEBNext® Ultra DNA Library Prep Kit for Illumina (NEB, USA). First, index codes will be added to sequences. Then, DNA sample will be fragmented into approximately 350 bp by sonication, then end-polished, A-tailed, and ligated with adaptors for Illumina sequencing via PCR. Lastly, PCR products with universal primers will be purified (AMPure XP system), with libraries analyzed for size distribution by Agilent2100 Bioanalyzer and quantified using real-time PCR; and 4) The clustering of index-coded samples will be performed on a cBot Cluster system. After cluster generation, DNA library will be sequenced on an Illumina PE150 platform, generating paired-end reads.

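### The host-read filter fixes a 200–400 bp insert window around a 350 bp target; it cannot improve removal of human reads and, if removal is by concordant pair, it retains some

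*Protocol article*

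**What the plan says.** Section 2.8.2 (Microbiome characterization) gives the host-removal step in full: "Host-derived reads will be filtered using Bowtie2.2.4 software with parameters: -end-to-end, --sensitive, -I 200, -X 400". The two insert limits are therefore fixed in the text.

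Section 2.8.1 describes the libraries to which the filter is applied. The input is whole blood: a CTAB lysis buffer "will be added to 250 μl of the whole blood and gently inverted". Before library construction, the "DNA sample will be fragmented into approximately 350 bp by sonication", and the "DNA library will be sequenced on an Illumina PE150 platform, generating paired-end reads". No SD or range of fragment length is given, although the library size distribution is to be measured on a Bioanalyzer.

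The same section explains why host removal matters. It begins: "Because the blood microbiome may be less than 5 % of the entire blood DNA". It then says that many bacterial assemblies "are contaminated by human DNA sequences, leading to false-positive results", and comments: "The latter issue is considered the biggest problem in the analysis and interpretation of blood microbiomes".

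After host filtering, section 2.8.2 assembles the reads, drops fragments under 500 bp, predicts genes, excludes genes with two or fewer mapped reads, and annotates with Kraken2, the NR database and an LCA algorithm. The legend to Fig. 3 plans a human organoid control to see whether human sequence is called bacterial. Under section 2.9 the primary outcome is the change in relative abundance of blood YDB DNA over five time points.

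**The concern.** Host filtering is the first defence against the error that the authors rank highest. A setting at this step should either help to remove human reads or be left out.

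The window is lopsided: 150 bp of room below the target length but only 50 bp above it. Sonication produces a spread of lengths, so some human pairs will exceed 400 bp. If the pipeline removes only pairs that align concordantly, those human pairs pass into assembly and annotation as non-host reads. Sequence that matches a human-contaminated bacterial assembly can then be called bacterial. Such false taxa can add noise to the blood profiles and, where they enter the gene catalogue, to the total on which relative abundance is based.

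**Working it through.** The article states no leakage figure, so there is nothing to reproduce. The check asks what the window can do and how large the effect could be.

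**Inputs from the article**
- Insert window: 200 to 400 bp (2.8.2).
- Target fragment length: about 350 bp (2.8.1).
- Microbial share of blood DNA, f: possibly below 5% (2.8.1). I use 5%, the most favourable value.

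**Assumptions**
- Insert length L is Normal(350, SD). The SD is not given, so I use 20 to 75 bp.
- The share of read pairs equals the share of DNA; all microbial pairs are kept, and all human pairs inside the window are removed.
- The behaviour of the limits is general knowledge of the software: -I and -X define concordance. Unless mixed and discordant alignments are switched off, other pairs are still searched as discordant or single-mate alignments. The article lists no option that switches them off.

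**Step 1: the two possible rules**
- Either-mate removal: a human pair outside the window is still removed through its aligned mates. The window has no effect.
- Concordance-only removal: a human pair outside the window is kept.

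Under neither rule does the window remove a human pair that would otherwise stay.

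**Step 2: share of pairs outside the window**

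Outside = P(L < 200) + P(L > 400), with z = (200 − 350)/SD and z = (400 − 350)/SD.

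| Assumed SD (bp) | Below 200 | Above 400 | Outside |
|---|---|---|---|
| 20 | 0.00% | 0.62% | 0.6% |
| 35 | 0.00% | 7.66% | 7.7% |
| 50 | 0.13% | 15.87% | 16.0% |
| 75 | 2.28% | 25.25% | 27.5% |

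Almost all of it is the long tail. The target is only approximate: at SD 50, a true mean of 300 bp gives 4.6% outside (split equally between the tails), and a mean of 400 bp gives 50%.

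**Step 3: human share of the retained reads**

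Host share = (1 − f) × outside × k / [(1 − f) × outside × k + f], where k is the fraction of outside-window human pairs that the rule keeps.

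With f = 0.05 and outside = 0.16:
- k = 1 (concordance-only): 0.95 × 0.16 = 0.152; 0.152 / (0.152 + 0.05) = 75%.
- k = 0.1: 0.0152 / 0.0652 = 23%.
- k = 0.01: 0.00152 / 0.05152 = 3%.
- k = 0 (either-mate): 0%.

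The result also depends on the spread. With k = 1 and SD 20: 0.95 × 0.0062 = 0.0059; 0.0059 / 0.0559 = 10.5%. A microbial share below 5% raises these figures: at an assumed f of 1%, with outside = 0.16 and k = 1, it is 0.1584 / 0.1684 = 94%.

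These are shares of reads leaving the host filter, before assembly and annotation. They are not shares of reads finally called bacterial.

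**The case against.** The strongest objection is that the article never says removal is by concordant pair. With the options listed, Bowtie2 would still find most outside-window human pairs as discordant or single-mate alignments, so the leak may be zero. An article may also leave the exact discard rule to the full protocol or to the published pipeline it cites. Both points stand: no leak is demonstrated, and the missing discard rule is not itself the finding. What remains is the parameter that the article does fix, which can only be neutral or harmful at this step.

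The second objection is that a leaked pair is not automatically counted as microbial. It must contribute to an assembled fragment of at least 500 bp, fall in a predicted gene with more than two mapped reads, and pass annotation. The organoid control is aimed at this error, and the study relies on defined species with newer assemblies. This reduces the harm considerably. It does not remove it, because human sequence matching a contaminated assembly is what annotation can miscall, and the article states no correction based on the organoid result.

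A reader might infer three stronger points, which the article does not support:
- **Circulating DNA is too short for the window.** The article says only that cmDNA is material "which consists of fragmented genetic material from microorganisms rather than intact, viable cells" and gives no length. The input is sonicated whole blood, and at SD 50 only 0.13% of pairs fall below 200 bp.
- **Leaked human reads would far outnumber microbial ones.** At SD 35 with full leakage and f = 5%, the comparison is 0.95 × 7.7% = 7.3% against 5%; at SD 20 it is 0.6% against 5%. A larger excess needs a wider spread or a microbial share that the article does not quantify.
- **Leakage would mimic a change over time.** Nothing links library size distribution to visit or to yogurt intake. Noise and false taxa are the more likely result.

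**Conclusion.** The concern holds in a limited form. The 200–400 bp window cannot improve human-read removal, and its upper limit is close enough to the 350 bp target to matter if removal depends on concordance. In that case 0.6% to 27.5% of human pairs would be retained over assumed SDs of 20 to 75 bp. In the 16% case, human reads would be about three quarters of what leaves the filter at a 5% microbial share. If either aligned mate triggers removal, the effect of this setting is zero.

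The conclusion that the window does not help rests on how the software treats the limits, not on the assumed SDs. The percentages rest on the normal model, the SDs, a mean of 350 bp and the retention rule, none of which the article settles. This is an avoidable weakness in a stated setting, not evidence that the primary result will be biased. It is worth correcting because it touches the problem that the authors themselves rank first.

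**What to change.** In section 2.8.2, remove -I 200 and -X 400 from the host-removal command. State that a pair is discarded when either mate aligns to the human reference, whatever the insert size or orientation. Apply the same rule to all participant samples (blood and feces, every visit), the spiked samples and the human-derived controls. Report residual human reads per library, with the organoid control as the benchmark.

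Suggested wording: *Read pairs will be discarded if either mate aligns to the human reference genome, irrespective of insert size or orientation; the same rule will be applied to all participant samples, spiked samples and human-derived controls, and residual human reads will be reported for each library.*

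The cost is one changed command and, if data have already been processed, a re-run from the filter step. The downside is a very small loss of true microbial pairs with a human-like mate. The spiked blood samples already planned allow that loss to be measured.

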#### Primary objective

2.5.1

The primary objective is to examine yogurt-dependent bacterial (YDB) DNA counts in fecal and blood samples before and after dairy consumption. YDB, such as *Lactococcus lactis*, are transient residents of the human gut, only present following dairy intake, and therefore represent modifiable components of the intestinal microbiome. Detection of YDB DNA fragments in the bloodstream after dairy reintroduction will provide definitive evidence on the extent to which the blood microbiome reflects relevant changes in the intestinal microbiome. In this specific study, the use of a commercial yoghurt (but verified by independent agar growth testing) containing a defined consortium of bacteria adds signature species whose detection provides convincing signals in this respect.

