### Statistical analysis

2.9

The primary outcome is the change in relative abundance of blood YDB DNA across five time points. This will be analyzed using repeated measures ANOVA to detect statistically significant within-subject changes over time. The secondary outcomes include changes in all other non-human microbial DNA, which will also be analyzed using repeated measures ANOVA. All statistical tests will be two-tailed, with significance set at p < 0.05.

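### Blood YDB is counted only on assembled genes (scaftigs of at least 500 bp, more than two mapped reads), which biases the primary outcome toward zero when YDB reads in blood are sparse

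*Protocol article*

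**What the plan says.** Section 2.9 defines the endpoint: "The primary outcome is the change in relative abundance of blood YDB DNA across five time points". Section 2.8.2, whose first step is headed for blood Lactococcus and other microbial DNA, gives one route to that quantity. Cleaned, host-filtered reads are assembled with MEGAHIT, and assembled pieces below 500 bp are dropped. Gene prediction starts only from what survives: "Scaftigs ≥500 bp will be analyzed for open reading frames (ORFs) using MetaGeneMark". A non-redundant gene catalogue is built, reads are mapped back, and a count filter follows: "Clean reads will be mapped to this catalogue using Bowtie2, and genes with ≤2 mapped reads will be excluded". Only then are the unigenes given a taxonomy and an abundance.

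The target is described differently. The Introduction says that circulating microbial DNA is "fragmented genetic material from microorganisms rather than intact, viable cells". Section 2.5.1 takes as its evidence "Detection of YDB DNA fragments in the bloodstream after dairy reintroduction". Section 2.8.1 warns that "the blood microbiome may be less than 5 % of the entire blood DNA" and discusses the difficulties of low biomass. For the library, the "DNA sample will be fragmented into approximately 350 bp by sonication", and it is read as paired-end 150 bp.

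Section 2.8.3 says that YDB will be analysed separately, but this comes after the taxonomic step and restores no discarded reads. Section 2.8.4 sends stool through the same pipeline. Section 2.8.1 and Fig. 3 add a dilution series of yogurt DNA spiked into participants' blood.

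**The concern.** Assembly with a length cut and a minimum read count suits stool, where a species is covered many times over. In blood, the species of interest may be represented by scattered fragments. A 350 bp insert cannot reach 500 bp alone, so several fragments from the same stretch of the same genome are needed before any gene exists to be counted. The count filter then requires at least three reads on that gene.

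The species to be found are known in advance, so their reads could be recognised without assembly. Under the written rules, a blood sample with a modest number of genuine YDB reads can be recorded as zero. The Abstract sets out to confirm or exclude circulating microbial DNA as a representative of the gut microbiome. Section 2.6 treats failure to show a *Lactococcus lactis* trend as a sign that blood microbiome studies may lack the power to show meaningful change. A zero made by the filter would feed directly into that reading. Partial detection is also distorted: abundance stays at zero until coverage crosses a threshold and then rises, which affects the comparison over the five time points.

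**Working it through.** The article states no detection limit, depth or expected YDB count, so there is no figure of its own to reproduce.

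**Inputs from the article.** Insert about 350 bp; reads 2x150 bp; scaftigs below 500 bp removed; genes with two or fewer reads removed; microbial share of blood DNA possibly below 5%.

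**Assumptions.** Genome 2-3 Mb; 2,000-3,000 genes; error-free reads placed at random; contigs joined at an overlap of at least 30 bp; N = YDB read pairs of one species in one sample. For step 2 the catalogue is assembled from that single blood sample.

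**Step 1: fragments needed for 500 bp.** A pair reads bases 0-150 and 200-350 of its insert, leaving 50 bp unread in the middle. A second pair shifted by 120 bp reads 120-270 and 320-470. All four reads then chain with at least 30 bp overlap and span 470 bp, the maximum for two pairs. Two pairs therefore fall short, and at least three are needed.

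**Step 2: length rule.** N pairs were placed at random and joined, and spans of at least 500 bp were counted. Coverage = N x 300 / genome length. Ranges are over 3 Mb to 2 Mb.

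| YDB pairs | Coverage | Chance of any contig of at least 500 bp | Share of YDB reads in such contigs |
|---|---|---|---|
| 10-30 | 0.001-0.0045x | about 0% | about 0% |
| 100 | 0.010-0.015x | about 0.2% | below 0.01% |
| 300 | 0.030-0.045x | 3-6% | below 0.1% |
| 1,000 | 0.10-0.15x | 65-89% | 0.3-0.7% |
| 10,000 | 1.0-1.5x | 100% | 24-43% |
| 50,000 | 5.0-7.5x | 100% | 98-100% |

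**Step 3: count rule alone.** Suppose the catalogue is complete and the rule acts per sample. If both reads of a pair fall on the same gene, one pair gives two reads and is dropped, and two pairs give four and are kept. A pair survives if at least one other pair hits its gene:

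share kept = 1 - exp(-N/genes)

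- N = 10: 1 - exp(-10/3,000) = 0.3%; 1 - exp(-10/2,000) = 0.5%
- N = 100: 3.3% to 4.9%
- N = 300: 9.5% to 13.9%
- N = 1,000: 28% to 39%

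**Step 4: where might N lie?** N = depth x microbial share x YDB share of microbial reads. With assumed depths of 20-100 million pairs, a microbial share of 0.01-5% and a YDB share of 0.1-1%:

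- low end: 20,000,000 x 0.0001 x 0.001 = 2 pairs
- high end: 100,000,000 x 0.05 x 0.01 = 50,000 pairs

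The range covers both near-total loss and almost none. Only the 5% comes from the article, and it is an upper bound.

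**The case against.** Four points weigh on the other side.

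- **Depth and abundance are unknown.** A reader might infer that the endpoint is zero wherever circulating microbial DNA is plausible, because one insert is shorter than 500 bp. The documents do not support that. They give no depth and no YDB count, the length rule acts on assembled scaftigs and not on raw fragments, and step 4 reaches counts at which almost everything is kept. This stands and makes the finding conditional.
- **The catalogue may be pooled.** Stool goes through the same pipeline, pooled yogurt DNA is sequenced, and Section 2.8.3 mentions a pooled dataset. If stool or yogurt contributes genes, short blood reads can map to them and most of the length loss disappears. Nor does the article say that the count rule acts per sample; applied to pooled reads it would bind less. Section 2.8.1 also allows a slightly modified version of a published pipeline. This stands too, but the article does not say that the catalogue is pooled and names no change to these filters.
- **The spike-in series is a safeguard.** Low dilutions that fail would probably expose the loss, and a null result could be read against a measured limit. However, no acceptance limit is given, and nothing ties the result to a change in the filters.
- **Strict filters protect specificity.** Section 2.8.1 ranks false positives from human sequence in bacterial assemblies as the main problem in this field. The trade-off is real, but length and count rules sort by abundance and not by origin: an abundant contaminant passes and a sparse true signal fails.

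**Conclusion.** The concern holds in conditional form. As written, the only described route to the primary outcome counts blood YDB after two filters that favour non-detection at low read counts.

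With a catalogue from a single blood sample, detection is very unlikely at 300 pairs or fewer. At 1,000 pairs it is likely, but on less than 1% of the YDB reads. At about 5x coverage or more the loss is negligible. With a pooled catalogue, the count rule applied per sample is the remaining loss: it is heavy up to a few hundred pairs and still removes well over half at 1,000.

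These figures rest on the assumed genome size, gene number and overlap, and on random placement of reads. They do not show that the trial will miss a true signal, and they support no single factor for the loss. They do show that a zero under these rules cannot be read as absence of YDB DNA unless the detection limit is known.

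**What to change.** For the primary blood YDB endpoint, count without assembly and without the two-read filter. Map host-depleted read pairs competitively to the genomes of the yogurt strains, their close relatives and human. Keep only uniquely assigned pairs, and require them to be spread over distinct loci. Set the positivity cut-off from the planned spike-in dilution series together with the unspiked and negative controls, and fix it before trial results are seen. Keep the assembly pipeline for stool and for the broader secondary profile.

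This uses reads that are generated anyway and needs no extra samples or sequencing, so the cost is some added analysis work. The downside is more false-positive read calls, which the uniqueness rule and the background cut-off limit but do not remove.
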